### 2.5. Questionnaire Survey

A parental questionnaire will be administered at the baseline and at the 18-month and 30-month follow-ups [19]. The baseline questionnaire will collect information about children’s oral-health-related behaviour (oral hygiene habits, the use of fluoride agent, parent-assisted tooth-brushing, dental visit behaviour, and snacking habits), and family background information (parental educational level, total family income and family status). The follow-up questionnaires will reassess the children’s oral health-related behaviour and measure parental satisfaction towards their children’s oral health status and appearance by five-point Likert scale. Parents will also be asked to report any potential complications or adverse events experienced by their child after the SDF application, such as tooth pain or gingival irritation.

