### 2.7. Randomisation, Treatment Allocation, and Allocation Concealment

Eligible children will be stratified based on the number of carious tooth surfaces at baseline (1 to 3 surfaces vs. more than 3 surfaces) and randomly allocated to receive either 38% SDF solution or gel. Block randomisation with a block size of 6 will be adopted to assign children to the two treatment groups. A statistician who is not involved in the clinical assessment will generate the randomisation sequence and place the group assignments in opaque sealed envelopes. During the clinical examination, once eligibility is confirmed, a research assistant will assign the randomisation envelope sequentially. This approach ensures effective allocation concealment prior to the administration of the assigned SDF intervention.

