### 2.13. Sample Size and Power Calculation

In our previous clinical trial, the proportion of active carious surfaces that became arrested after the biannual application of 38% SDF solution over 24 months was 76.5% [25]. We set the non-inferiority margin at 7.65% (which corresponds to 10% of the caries arrest rate observed with the SDF solution). This non-inferiority margin represents a difference between the intervention products that we consider to be clinically insignificant. The estimated sample size is based on the lower limit of the two-sided 95% confidence interval for the difference being set above the non-inferiority margin (−7.65%) and the statistical power of the study being set at 90% (β = 0.10) by the Sealed Envelope Power (sample size) calculators [26].

This non-inferiority trial requires 1292 active-caries tooth surfaces at the 30-month follow-up assessment. We have accounted for the fact that each child may present with multiple carious tooth surfaces, with an estimated mean of 4.75 active-carious surfaces per child and an intraclass correlation (ICC) of 0.227, based on our previous study findings [25]. Furthermore, we have estimated a 30-month dropout rate of 20% and an ECC prevalence of 38% among 3-year-old children, according to the available epidemiological data [27]. Therefore, we will screen approximately 3000 3-year-old children to recruit at least 630 children with ECC, with 315 children assigned to each of the two SDF intervention groups.

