### 2.15. Statistical Analysis

Data analysis will be conducted using SPSS 24.0 software (SPSS Inc., Chicago, IL, USA). Intra-examiner agreement for caries diagnosis will be evaluated using Cohen’s Kappa statistics. Non-inferiority of the SDF gel group compared with the SDF solution group (control, caries arresting rate 76.5%) will be accepted if the lower limits of the 95% two-sided CI of the difference in the caries-arresting rate is greater than the non-inferiority margin (7.65%). This test for non-inferiority will only be performed for the primary endpoint, which is the proportion of the soft (active) carious tooth lesion surfaces that turn hard (arrested) at the 30-month follow-up. An intention-to-treat approach is planned to utilise all available data from all originally recruited children.

At subject level, chi-square tests will be used to compare proportions of arrested carious surfaces between groups during the follow-ups. These statistical tests will also be applied to analyse the incidence of new carious surfaces and dropout rates between groups during the follow-ups. Independent sample t-tests will be employed to investigate the differences in the mean values of continuous outcome measures, including the number of newly developed carious surfaces, dmfs scores, and non-vital/hypermobile teeth. Descriptive analyses will be used to report the proportions of adverse effects, as well as the levels of child and parental acceptance for each intervention. The McNemar test will be used to compare the changes in oral-health-related behaviours and children’s cooperation between different treatment groups.

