A multilevel logistic regression model will be employed to account for the clustering effect of multiple carious lesions within individuals. This multilevel model will assess the effectiveness of 38% SDF gel versus 38% SDF solution in arresting active caries at 6, 12, 18, 24 and 30 months, adjusting relevant covariates, such as social-demographic background, oral health-related behaviours, baseline oral characteristics and daily fluoride exposure. By employing this multilevel analytical framework, the study will provide robust evidence on the efficacy of the 38% SDF gel in managing ECC among preschool children. All hypothesis tests will be two-tailed with an α = 0.05 significance level, and they will be conducted according to the pre-specified analyses, adhering to the intention-to-treat principles. Sensitivity analyses will be performed to address any missing data.

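### The planned t-tests ignore baseline dmfs and the stratification factor, and the stratum is not named for the non-inferiority comparison: precision is lost, validity is not

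*Protocol article*

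**What the plan says.** All references are to the protocol article.

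- **Supporting outcomes.** Section 2.15: "Independent sample t-tests will be employed to investigate the differences in the mean values of continuous outcome measures". The named outcomes are new carious surfaces, dmfs and non-vital or hypermobile teeth. No baseline value and no stratum enters the test.
- **Baseline data.** Section 2.6 has dmfs recorded at the examination. Section 2.12 has the same examiner repeat it every six months with unchanged criteria.
- **Randomisation.** Section 2.7: "Eligible children will be stratified based on the number of carious tooth surfaces at baseline (1 to 3 surfaces vs. more than 3 surfaces").
- **Non-inferiority rule.** Section 2.15 compares the lower bound of a 95% interval for the arrest-rate difference with the 7.65-point margin. It names neither a method for the interval nor the stratum.
- **Multilevel model.** Section 2.15 adds a logistic model that allows for clustering within children, "adjusting relevant covariates, such as social-demographic background, oral health-related behaviours, baseline oral characteristics and daily fluoride exposure". It is not tied to the margin.
- **Behaviours.** Section 2.5 places questionnaires at baseline, 18 and 30 months. "The follow-up questionnaires will reassess the" behaviours already asked about at baseline.
- **Outcome list.** Section 1.5 gives parental satisfaction, compliance and adverse effects as secondary outcomes. None of the t-tested measures is among them.

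**The concern.** dmfs counts decayed, missing and filled surfaces, so a follow-up score carries much of the baseline score forward. A plain t-test treats that known spread between children as noise, and the interval for the arm difference is wider than the data require.

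Stratified allocation makes the arms alike on baseline lesion count. An analysis that ignores the stratum does not credit this and reports a standard error slightly too large. For the supporting outcomes the stake is the width of the intervals; for the primary comparison it is a little power.

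A smaller matter is the covariate list. It attaches the word baseline to oral characteristics only, while behaviours are measured again after randomisation. Adjusting a randomised comparison for values that treatment may have influenced can bias it, so the timing should be stated.

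**Working it through.** **Inputs from the documents.** Section 2.13: "biannual application of 38% SDF solution over 24 months was 76.5" per cent in the control arm; margin 7.65 points; two-sided 95% interval (one-sided 0.025); power 90%; 4.75 surfaces per child; ICC 0.227; dropout 20%; 630 children, 315 per arm. Section 2.7: strata of 1 to 3 and more than 3 surfaces.

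**Assumptions, because the documents give no figure.** Correlation ρ between baseline and follow-up dmfs: 0.3 to 0.8. Difference d in arrest rate between strata: 5 to 20 points. Share w of the weight in one stratum: 0.3 or 0.5.

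**Step 1. The plan's own figures.** Per arm, n = (1.960 + 1.282)² × 2 × 0.765 × 0.235 / 0.0765² = 646 after rounding up, so 1292 surfaces in all. Design effect = 1 + (4.75 − 1) × 0.227 = 1.851. Then 1292 × 1.851 = 2392 surfaces; 2392 / 4.75 = 503.5 children; 503.5 / 0.80 = 629.4, so 630. Both stated figures reproduce. They assume no covariates, so adjustment does not undermine them.

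**Step 2. The t-test on follow-up dmfs.** Adjusting for baseline multiplies the variance by 1 − ρ². For a difference the t-test would detect with 80% power, power becomes Φ[(1.960 + 0.842)/√(1 − ρ²) − 1.960].

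| ρ (assumed) | variance ratio | variance removed | SE ratio | 80% power becomes |
|---|---|---|---|---|
| 0.3 | 0.91 | 9% | 0.954 | 83.6% |
| 0.5 | 0.75 | 25% | 0.866 | 89.9% |
| 0.7 | 0.51 | 49% | 0.714 | 97.5% |
| 0.8 | 0.36 | 64% | 0.600 | 99.7% |

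For new surfaces and non-vital teeth the documents give nothing from which to size the gain, and none is claimed.

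**Step 3. The stratum in the primary comparison.** The variance of a child's arrest proportion is about 0.765 × 0.235 × 1.851 / 4.75 = 0.0701. The part due to strata is w(1 − w)d². The SE ratio is the square root of 1 minus the quotient of the two. Nominal 90% power becomes Φ[(1.960 + 1.282)/SE ratio − 1.960].

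| d (assumed) | SE ratio, w = 0.3 | SE ratio, w = 0.5 | power, w = 0.5 |
|---|---|---|---|
| 5 points | 0.996 | 0.996 | 90.3% |
| 10 points | 0.985 | 0.982 | 91.0% |
| 15 points | 0.966 | 0.959 | 92.2% |
| 20 points | 0.938 | 0.926 | 93.8% |

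The SE falls by about 0.4% to 7%.

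**Step 4. Direction of the error.** A simulation used 252 children per arm (315 × 0.80), half in each stratum, with assumed counts of 1 to 3 and 4 to 11 surfaces, ICC 0.227, no true arm difference and 4000 repetitions.

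| d | actual SD, unadjusted | mean SE, unadjusted | mean SE, stratified | power gained |
|---|---|---|---|---|
| 0 | 0.02643 | 0.02652 | 0.02655 | 0.1 points |
| 10 points | 0.02686 | 0.02694 | 0.02679 | 0.4 points |
| 20 points | 0.02709 | 0.02764 | 0.02695 | 1.8 points |

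At 20 points the unadjusted SE exceeds the actual spread by 2.0% (0.02764/0.02709), so ignoring the stratum errs on the cautious side. Simulated power is below 90% throughout because the assumed counts vary between children; only the comparison within a row bears on this point.

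**Step 5. Covariate timing.** Section 2.5 collects behaviours and fluoride use at baseline, and behaviours again later. The covariate list in Section 2.15 does not say which measurement is meant. The text permits either reading and commits to neither.

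**The case against.** A reader might infer that the non-inferiority analysis is unadjusted and its interval wrong. The documents do not show this. Section 2.15 gives a decision rule without a method for the interval, and a condensed article may leave that to an analysis plan not shown. The stratum is therefore not named, rather than shown to be left out. The multilevel model's baseline oral characteristics could also include it. That stands in part: the model is logistic, gives an odds ratio unless converted, and is not linked to the margin.

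A reader might also infer that the model will adjust for behaviour measured after randomisation. No passage says so. Baseline values exist for the behaviours, the repeat measurements have their own use in the planned comparison of behaviour changes, and parents and children are blinded. Only a clarification remains.

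On the t-tests, the other side can say that randomisation keeps them unbiased, that these outcomes are not listed in Section 1.5, and that the size rests on an assumed correlation. All three hold, and they limit the weight of the point. It can also be said that dmfs scores might mean increments. Then, with equal variances at both times, the variance ratio of adjusted to change-score analysis is (1 − ρ²)/[2(1 − ρ)] = (1 + ρ)/2, or 0.65 at ρ = 0.3 and 0.90 at ρ = 0.8. The gain is then 35% down to 10%, so the point survives either reading. The t-tests are named outright and so are not a detail left for later.

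**Conclusion.** The point holds as one of efficiency. The plan fixes unadjusted t-tests although baseline dmfs and the stratum are at hand. For dmfs the loss is 9% to 64% of the variance of the follow-up comparison, entirely conditional on an assumed correlation of 0.3 to 0.8, and it falls on supporting outcomes.

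For the primary comparison the stratum is not named. Including it would lower the SE by about 0.4% to 7% under assumed stratum differences of 5 to 20 points, and by 0.6% and 2.5% in the simulation at 10 and 20 points. Leaving it out is slightly conservative, so a false claim of non-inferiority does not become more likely. The t-tests are not invalid, and the 1292 surfaces and 630 children stand. Covariate timing is a request for clarification, not an error.

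**What to change.** - Replace the t-tests with regression on arm, adjusted for stratum (1 to 3 or more than 3 surfaces) and baseline dmfs. A count model for new surfaces and non-vital teeth is optional.
- Name the stratification factor in the child-clustered risk-difference analysis that yields the interval compared with the 7.65-point margin.
- As a clarification, state that behaviour and fluoride covariates in the multilevel treatment-effect model are baseline values.

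The cost is wording in the analysis plan, best settled before the database is locked. It needs no new data, extra visits or change in sample size.

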### 1.5. Outcome Measures

The primary outcome is the proportion of soft (active) carious tooth surfaces that turn hard (arrested) at the 30-month follow-up. The secondary outcomes are parental satisfaction, children’s compliance, and adverse effects of the SDF therapy.

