However, direct comparative evidence on the caries-arresting capacity and clinical efficacy of SDF gel versus the traditional SDF solution is limited. To address this evidence gap, this randomised controlled trial will employ a non-inferiority design to evaluate whether the SDF gel formulation is at least as effective as the standard SDF solution in arresting dental caries. We selected a 10% non-inferiority margin based on the existing literature and practical considerations in paediatric dentistry [33]. This margin allows us to assess clinical relevance while accommodating the challenges associated with sample size in the community. Given that this clinical trial requires the screening of approximately 3000 preschool children, the chosen margin strikes a balance between ensuring meaningful clinical outcomes and maintaining the feasibility of the trial. Furthermore, SDF gel may potentially offer additional benefits, such as improving application precision, reducing soft tissue staining, and enhancing patients’ acceptability. This study has large sample size which will provide adequate statistical power to detect any non-inferiority of the SDF gel compared to the SDF solution. Demonstrating the non-inferiority of SDF gel could support its clinical use, especially for paediatric patients among whom the precisely application of SDF therapies and extended contact time of the agents are prioritised. SDF gel also retains other advantages of SDF, such as affordability, accessibility, minimal invasiveness, and non-aerosol generation, making it an attractive option for public-health-oriented caries prevention and management strategies.

Overall, this study aims to provide robust clinical evidence on the effectiveness of 38% SDF gel in managing ECC. Confirming its non-inferiority to traditional SDF solution would promote its adoption, especially in public health contexts focused on paediatric oral care. The SDF gel’s affordability, ease of use, and minimal invasiveness offer a promising tool for advancing caries prevention strategies and improving children’s oral health worldwide.

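### Adverse effects and parental satisfaction are declared secondary outcomes, but Section 2.15 plans only description by arm, with no between-arm difference or confidence interval

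*Protocol article*

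**What the plan says.** Section 1.5 of the protocol article lists three secondary outcomes: "The secondary outcomes are parental satisfaction, children’s compliance, and adverse effects of the SDF therapy".

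Section 2.15 gives the method for two of them: "Descriptive analyses will be used to report the proportions of adverse effects, as well as the levels of child and parental acceptance", separately by intervention. For the third, compliance, it says: "The McNemar test will be used to compare the changes in oral-health-related behaviours and children’s cooperation between different treatment groups". The non-inferiority comparison is confined to arrest: "This test for non-inferiority will only be performed for the primary endpoint".

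The same paragraph of Section 2.15 plans chi-square tests between groups for arrested surfaces, for the incidence of new carious surfaces and for dropout. It plans independent-sample t-tests for continuous measures, "including the number of newly developed carious surfaces, dmfs scores, and non-vital/hypermobile teeth".

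On rationale, Section 1.2 describes spillage and staining with the solution as the problem that the gel was developed to solve, and notes that satisfaction, compliance and adverse effects of the two therapies have not been studied. The Discussion says: "SDF gel may potentially offer additional benefits, such as improving application precision, reducing soft tissue staining", and adds acceptability.

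On data, Sections 2.11 and 2.12 have an independent practitioner examine every child one day after therapy for pain, allergic reaction, gingival irritation and soft-tissue staining. Section 2.5 measures parental satisfaction on a five-point Likert scale at 18 and 30 months.

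**The concern.** The protocol does not leave the analysis of these two outcomes open. It chooses description per arm. Measures absent from the list of secondary outcomes (new carious surfaces, dmfs, non-vital or hypermobile teeth) do get between-group tests. The order of priority in Section 1.5 and the analyses in Section 2.15 therefore do not match.

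This matters because readers of a non-inferiority trial will want to know what else distinguishes the new product. If less staining or higher satisfaction is reported with the gel, there will be no pre-specified estimate behind the statement. If a harm is more frequent with the gel, there will be no planned interval to show how large the excess could be. In both cases someone will choose the comparison after seeing the data.

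**Working it through.** **1. The declared secondary outcomes against their planned analyses.**

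| Outcome in Section 1.5 | Analysis in Section 2.15 | Between-arm comparison planned? |
|---|---|---|
| Adverse effects | Descriptive proportions by intervention | No |
| Parental satisfaction | Descriptive levels of parental acceptance by intervention | No |
| Children's compliance | Description of child acceptance; McNemar test named as a between-group test | Named, but McNemar is a test for paired data |

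This reads parental acceptance in Section 2.15 as the satisfaction measure of Section 2.5, the only parental rating that the article describes.

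**2. The plan's own sample size.** No figure is stated for the secondary outcomes, so the check is that the primary figure is sound and that the numbers per arm can be relied on. Inputs from Section 2.13: arrest rate 76.5%, margin 7.65 points, two-sided 95% interval, 90% power, 4.75 surfaces per child, ICC 0.227, 20% dropout.

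- Surfaces per arm: (1.96 + 1.2816)² × 2 × 0.765 × 0.235 / 0.0765² = 645.5, so 646 per arm and 1292 in all, as stated.
- Design effect: 1 + (4.75 − 1) × 0.227 = 1.851.
- Children: 1292 × 1.851 / 4.75 = 503.5; 503.5 / 0.80 = 629.4, so 630, as stated.

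The trial therefore has 315 children per arm at entry and 315 × 0.80 = 252 at 30 months.

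**3. What a planned comparison would deliver.** The documents give no rates for harms or satisfaction, so the rates p below are assumptions. With about the same rate in both arms and each child counted once, the 95% half-width is 1.96 × √(2p(1 − p)/n).

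| Assumed rate | Half-width, n = 252 per arm |
|---|---|
| 2% | ±2.4 points |
| 5% | ±3.8 points |
| 10% | ±5.2 points |
| 20% | ±7.0 points |
| 50% | ±8.7 points |

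Example at 10%: 1.96 × √(0.18/252) = 0.052. With all 315 per arm, the range from 2% to 50% is ±2.2 to ±7.8 points. At 2% only about 5 events per arm are expected (0.02 × 252), so the normal approximation is rough there and an exact interval is preferable.

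For a satisfaction score in standard-deviation units, the half-width is 1.96 × √(2/252), about 0.17 SD.

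These intervals are narrow enough to be informative. The gap lies in the planned method, not in the amount of data.

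**The case against.** The strongest reply has four parts.

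- **Descriptive reporting of harms is common, and no superiority hypothesis on harms or satisfaction is stated.** This stands. It is why the remedy is estimation and not a confirmatory test.
- **The article is condensed, so detail may sit elsewhere.** This stands for details such as whether a proportion counts children, visits or applications. A reader might infer that repeated harm checks on the same child will be pooled naively; the text does not say so. The reply does not cover the main point, because the article itself states the method as descriptive.
- **The t-test sentence introduces its list as non-exhaustive, so a Likert score might fall under it.** This is possible but strained, since the next sentence assigns acceptance to description. It would not help adverse effects.
- **The trial can still speak on these outcomes.** A reader might infer that it cannot say whether the gel is better or worse. That goes too far: randomised arms reported separately let anyone compute a crude difference and interval. What is absent is a comparison fixed in advance.

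A reader might also infer that the case for the gel rests on these outcomes, or that they are meant to offset a tolerated loss of arrest. The documents do not support this. The objective and hypothesis (Sections 1.3 and 1.4) concern arrest alone, and the Discussion calls the other benefits potential and additional and describes no trade-off. Nor do formal tests go only to undeclared outcomes: arrested surfaces are tested, and children's cooperation has a named between-group test. That the McNemar test does not suit independent arms is a separate matter.

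**Conclusion.** The point holds in a limited form. Two of the three declared secondary outcomes, both part of the stated rationale, are assigned per-arm description with no pre-specified difference or interval, while outcomes outside the declared list are formally compared. A claim in either direction on harms or satisfaction would lack a planned comparison.

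The primary conclusion, the sample size (which reproduces exactly) and data collection are not affected. The size of the gap can only be illustrated: about ±2.4 to ±8.7 percentage points for a risk difference with 252 children per arm. This rests on assumed rates of 2% to 50%, the plan's own 20% dropout, and one observation per child. A change is worthwhile because the comparison is cheap and the data will already exist.

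**What to change.** Amend Section 2.15 as follows.

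- **Adverse effects.** For each harm type (pain, allergic reaction, gingival irritation, soft-tissue staining), report the number and proportion of children ever affected by arm, with the risk difference and 95% confidence interval at child level. Where events are frequent enough, add an estimate over all applications clustered by child, for example by GEE. Where events are rare, give counts with exact intervals, since a model-based risk difference may not be estimable.
- **Parental satisfaction.** For the five-point items at 18 and 30 months, report a between-arm estimate with 95% confidence interval from an ordinal model with arm and randomisation stratum.
- **Status.** Label all of these as secondary estimates without a confirmatory claim.

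If description alone is kept, the plan should say that conclusions on these outcomes will stay descriptive.

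The cost is a few lines of text and a little more analysis. No new data, visits or participants are needed.

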## 2. Methods/Design

### 2.1. Trial Design

This is a 30-month single-centre randomised, active-controlled, parallel-group non-inferiority pragmatic clinical trial with two arms. It follows the Standard Protocol Items: Recommendations for Interventional Trials (SPIRIT) 2013 Statement [18]. Figure 1 shows the trial’s schedule of enrolment, interventions, and assessments. and Supplementary Materials present the SPIRIT 2013 Checklist: Recommended items to address in a clinical trial protocol and related documents.

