### 2.10. Assessment of the Children’s Compliance

A trained research assistant will assess the children’s compliance during SDF therapy (solution or gel) using Venham’s behaviour-rating scale. This validated instrument provides six scores to evaluate a child’s reactions and behaviours during dental care [23]. Table 1 shows the codes of Venham’s behaviour-rating scale.

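### McNemar's test is assigned to a gel-versus-solution comparison of children's cooperation and oral-health behaviours, which a paired within-child test cannot make

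*Protocol article*

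**What the plan says.** Section 2.15 (Statistical Analysis) assigns one test to two sets of data: "The McNemar test will be used to compare the changes in oral-health-related behaviours and children’s cooperation between different treatment groups".

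The design sections define the groups being compared. Section 2.1 describes a "randomised, active-controlled, parallel-group non-inferiority pragmatic clinical trial with two arms". Under Section 2.7, children are stratified by number of carious surfaces and "randomly allocated to receive either 38% SDF solution or gel", in blocks of 6. Each child gets one formulation, and no child in one arm is matched to a child in the other.

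On the outcome, Section 1.5 states: "The secondary outcomes are parental satisfaction, children’s compliance, and adverse effects of the SDF therapy". Section 2.10 measures compliance with Venham's scale: "This validated instrument provides six scores to evaluate a child’s reactions and behaviours during dental care". Table 1 gives these as ordered levels 0 to 5, and Section 2.12 repeats the rating at follow-up. Behaviours come from the parental questionnaire at baseline, 18 and 30 months (Section 2.5).

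The only other analysis in Section 2.15 that touches child acceptance is descriptive: "Descriptive analyses will be used to report the proportions of adverse effects, as well as the levels of child and parental acceptance for each intervention".

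**The concern.** The sentence states a between-arm question and names a test that has no between-arm component. McNemar's test needs pairs, and the only pairs in this trial are two readings on the same child. It can therefore say whether something changed over time within a set of children, but not whether the change differs between gel and solution.

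What is at stake is the inference on one named secondary outcome, children's compliance, and on the questionnaire behaviours, which Section 1.5 does not list as an outcome. The Discussion suggests that gel may be more acceptable to children and useful where cooperation is difficult, and compliance is the outcome closest to that suggestion. Section 2.15 also commits hypothesis tests to the pre-specified analyses, so a method substituted after unblinding would be open to the charge of being chosen post hoc.

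**Working it through.** **1. Does another part of the plan supply the comparison?** Going through Section 2.15:
- Chi-square tests cover arrested surfaces, new carious surfaces and dropout.
- t-tests cover number of new surfaces, dmfs, and non-vital or hypermobile teeth.
- The multilevel logistic model covers caries arrest; behaviours enter it only as covariates.
- Adverse effects and acceptance are described by arm.

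McNemar is therefore the only test stated for cooperation or for behaviours.

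**2. What the statistic uses.** With b children positive only at the first reading and c positive only at the second, z = |b − c| / √(b + c). Arm appears nowhere. A between-arm test of change uses d = (c − b)/N in each arm, variance v = ((b + c)/N − d²)/N, and z = |d_A − d_B| / √(v_A + v_B).

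**3. Illustration.** N per arm = 315 × (1 − 0.20) = 252, from the recruitment target and dropout in Section 2.13. The documents give no rates for cooperation or behaviours, so the rates below are assumptions. Percentages are from 20,000 simulated trials at two-sided 0.05; z values are at expected counts.

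*(a) Same change in both arms, 60% to 70%* (10% positive only first, 20% only second):
- Each arm: z = (50.4 − 25.2)/√75.6 = 2.90, significant in about 84% of trials.
- Exactly one arm significant: about 2 × 0.84 × 0.16 = 0.27; simulated 26.5%. With a change from 65% to 70% (15% and 20% discordant) it is 39.5%.
- Pooled over arms: z = (100.8 − 50.4)/√151.2 = 4.10; significant in 98.6%.
- Between-arm test of change: 5.2%, the nominal level.

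*(b) Opposite changes, +10 and −10 points:*
- Pooled: b = c = 75.6, so z = 0; significant in 4.6%.
- Between-arm test: z = 0.20/√(2 × (0.30 − 0.01)/252) = 0.20/0.048 = 4.17; significant in 98.7%.

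*(c) Steady cooperation, 60% v 75%, no change over time:*
- McNemar, within either arm or pooled: about 5%.
- Two-sample comparison at one visit: z = 0.15/√((0.60 × 0.40 + 0.75 × 0.25)/252) = 0.15/0.041 = 3.64; power 95%.

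Pattern (c) is plausible here. Section 2.10 rates compliance while the assigned product is being applied, so an effect of formulation could already be present at the first application and would not appear as change.

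**4. Fit to the data.** Venham has six ordered levels at repeated visits, and the questionnaire has three time points. Classical McNemar takes a binary outcome at two. Section 2.15 states no cut-point and no pair of visits.

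**5. The plan's own figures.** A control rate of 76.5%, a margin of 7.65 points, one-sided 0.025 and 90% power give 646 surfaces per arm, so 2 × 646 = 1292 as stated. The design effect is 1 + (4.75 − 1) × 0.227 = 1.851. Then 1292 × 1.851/4.75 = 503.5 children, and 503.5/0.80 = 629.4, rounded up to the stated 630. None of this depends on the McNemar sentence.

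**The case against.** The best defence is that the word for change in the sentence points to within-child change over time, examined in each arm separately, for which McNemar is a proper test of binary items. It could be repeated for each follow-up against baseline, and extensions exist for more than two categories. This is a fair guess at the intention. But the text says the comparison is between treatment groups, and under the kinder reading cooperation would still have no between-arm test. No extension to more visits or categories brings arm into the statistic.

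A reader might go further and make three inferences that the documents do not support:
- *That no secondary outcome has a valid between-arm estimate.* Adverse effects and acceptance are to be reported by randomised arm. Such proportions are valid and their difference can be read directly. Description is a legitimate choice for secondary outcomes, and intervals or models may sit in an analysis plan that is not shown.
- *That the suggested advantage in soft-tissue staining could not be examined.* Staining is recorded one day after treatment by an independent practitioner (Section 2.11) and falls under adverse effects, to which McNemar is not assigned.
- *That information will be lost by dichotomising Venham and dropping visits.* The plan states neither step.

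It also stands that the objective and hypothesis concern caries arrest alone, and that the simulated percentages show the principle rather than the impact in this trial.

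**Conclusion.** The point holds as a wrongly assigned test. As written, Section 2.15 cannot deliver a gel-versus-solution comparison of children's cooperation, a named secondary outcome, or of change in oral-health behaviours. Applied within arms and contrasted, or pooled, the test can suggest arm differences that are absent and miss ones that are present. How often depends on rates the documents do not give.

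This assumes that cooperation in Section 2.15 means the compliance rated by Venham's scale in Section 2.10, which the wording of Table 1 supports. The primary non-inferiority analysis, the sample size and the descriptive reporting of satisfaction and adverse effects are untouched. It should be corrected before unblinding, but it does not threaten the trial's main conclusion.

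**What to change.** Replace the sentence in Section 2.15 with three statements:
- **McNemar:** limited to within-arm change over time in binary behaviour items, with the two time points named.
- **Venham score between arms:** a named method that uses arm. One option is an ordinal mixed model or GEE over all visits, with arm, visit and arm by visit, and child as the cluster. A simpler one is a rank or ordinal comparison at a set visit. If the model is used, state which arm contrast is reported; an arm-by-visit term alone would miss a steady difference.
- **Behaviour change between arms:** a logistic mixed model or GEE with an arm-by-time term over baseline, 18 and 30 months.

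Any valid between-arm method would repair the error; these are examples. The cost is a wording change and routine analysis of data the trial already plans to collect, with no new visits and no change in sample size.
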